### Power calculation

The sample size was calculated using STATA, based on clinically relevant differences. Effect Sizes (ES) are calculated as the difference between the control group and the intervention group after the intervention, divided by the pooled standard deviation [30]. With 100/100 patients the study is powered to detect an ES of 0.35 (one-sided), with a power of 80% (α = 0.05). Based on a meta-analysis [23], we may expect an ES of 0.5 to 0.6 [18]. We anticipate 30% non-completion/exclusion, which will be compensated by over sampling (n = 286; 143 in each group).

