**Methods/Design:**

The effectiveness of a web-based self-help course for adults with diabetes with co-morbid depression will be tested in a randomised trial, using a wait-list controlled design. The intervention consists of an 8-week, moderated self-help course that is tailored to the needs of persons living with diabetes and is offered on an individual basis. Participants receive feedback on their homework assignments by e-mail from their coach. We aim to include 286 patients (143/143), as power analyses showed that this number is needed to detect an effect size of 0.35, with measurements at baseline, directly after completing the web-based intervention and at 1, 3, 4 and 6 months follow-up. Patients in the control condition are placed on a waiting list, and follow the course 12 weeks after randomisation.

Primary outcomes are depressive symptoms and diabetes-specific emotional distress. Secondary outcomes are satisfaction with the course, perceived health status, self-care behaviours, glycaemic control, and days in bed/absence from work. Questionnaires are administered via the Internet.

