### Aims of the Trial

This study aims to test the effectiveness and appreciation of web-based cognitive behavioural therapy (W-CBT) for adult diabetes patients with depression in a randomized controlled trial. The experimental condition will be compared with a waiting-list control group. It is hypothesized, that W-CBT will be well-received by the participants and will appear to be significantly more effective than the control condition in reducing levels of depressed mood and diabetes-specific emotional distress, with subsequent positive effects on self-management behaviours and glycaemic control on the longer term.

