### Statistical Analyses

Analyses will be conducted according to the intention to treat principle. The data will be presented as categorical and continuous variables. Baseline characteristics will be compared for the intervention and waiting-list group using Student *t*-tests and χ^2^-tests. Analysis of variance (ANOVA) will be conducted with the CES-D (depression) as dependent variable, with two independent variables: time (within-subject) and group (between-subject). The same analysis will be performed with the PAID score (diabetes-related emotional distress) as dependent variable. Two analyses will be conducted. Firstly, the direct effect of the intervention will be determined. ANCOVA's will be performed in order to test whether both groups have different scores on the CES-D, at different points in time, with correction for potential confounders at baseline. Secondly, pre-post measurements will be conducted of all participants who have received the intervention. This will be analysed by means of a longitudinal regression analysis, which will be performed using Generalized Estimating Equations (GEE) [29], taking into account the correlational nature of repeated measures data within subjects, and securing minimal loss of patients due to incomplete data. Clinical effectiveness will be calculated by the amount of people who after completion of the course have a score on the CES-D of <16. The effect size will be calculated using Cohen's *d *[30].

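### The 80% power for an effect size of 0.35 belongs to a one-sided 5% test, but the analyses described are non-directional; two-sided, with 100 analysed per arm, power is about 69%

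*Protocol article*

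**What the plan says.** The Power calculation section of the protocol article defines the effect size as the post-intervention difference between arms divided by the pooled standard deviation. It then says: "With 100/100 patients the study is powered to detect an ES of 0.35 (one-sided), with a power of 80"%, with alpha 0.05. The same section expects a larger effect, 0.5 to 0.6, and raises 100 to 143 per arm (286 in total) to allow for 30% non-completion or exclusion.

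The Statistical Analyses section specifies intention to treat. For the primary outcome, "Analysis of variance (ANOVA) will be conducted with the CES-D (depression) as dependent variable", with time and group as factors, and ANCOVAs are planned "to test whether both groups have different scores on the CES-D, at different points in time, with correction for potential confounders at baseline". It gives neither an alpha nor a sidedness.

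The Aims section words the hypothesis directionally: the course "will appear to be significantly more effective than the control condition". The abstract says of the 286 patients that "power analyses showed that this number is needed to detect an effect size of 0.35" and does not mention that the calculation is one-sided. The Strengths and Limitations section calls the trial sufficiently powered for conclusions up to six months.

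**The concern.** The sample size rests on a one-sided 5% test, while the analysis is described as a test for a difference by ANOVA and ANCOVA. Their F-tests reject for a difference in either direction. If the trial is analysed as described, at the usual two-sided 5%, the quoted power is not the power of that test. With 100 analysed per arm, a true effect of 0.35 would be missed about 31% of the time, not 20%. If significance is instead judged one-sided at 5%, the chance of falsely favouring the course is 5%, against 2.5% under a two-sided 5% test. A reader of the abstract cannot tell which applies.

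A second question follows from intention to treat. Dividing by 0.70 treats the 30% as absent from the analysis. Patients who stop the course but are still measured stay in the analysis, and they may reduce the average effect instead of reducing n.

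**Working it through.** **Inputs from the article.** Alpha 0.05, effect size d = 0.35, expected d = 0.5 to 0.6, 100 per arm, 30% allowance and 143 per arm randomised (Power calculation); intention to treat (Statistical Analyses). The effect size is standardised, so SD = 1. The check treats the post-intervention comparison as a two-group contrast with one degree of freedom, matching the article's definition of the effect size.

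**Formulas (normal approximation).** Power = Φ(d·√(n/2) − z), with z = 1.645 one-sided and 1.960 two-sided. The n per arm for 80% power is 2(z + 0.842)²/d². The detectable effect is (z + 0.842)·√(2/n).

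**1. The plan's own figure, one-sided.**
- d·√(n/2) = 0.35 × √50 = 2.475.
- Power = Φ(2.475 − 1.645) = Φ(0.830) = 79.7% (noncentral t: 79.4%).
- n for 80% = 2 × 2.487²/0.1225, which rounds up to 101 (t: 102), against the stated 100.
- 100/0.70 = 142.9, so 143 per arm and 286 in total.

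The stated figures reproduce.

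**2. Same numbers, two-sided 5%.**
- Power = Φ(2.475 − 1.960) = Φ(0.515) = 69.7% (t: 69.2%).
- Detectable effect at 80% = 2.802 × √0.02 = 0.396 (t: 0.398), so about 0.40.
- n for d = 0.35 = 2 × 2.802²/0.1225, which rounds up to 129 (t: 130) analysed per arm. With the same 30% allowance, 129/0.70 gives 185 randomised per arm.

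**3. Intention to treat with all 143 per arm analysed, two-sided.** √(143/2) = 8.456. The diluted rows are assumptions; the article gives no such figures.

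| Average effect | Assumption | Two-sided power |
|---|---|---|
| 0.35 | no dilution | Φ(2.960 − 1.960) = 84.1% (t: 83.9%) |
| 0.2975 | 85% of 0.35 | 71.1% |
| 0.28 | 80% of 0.35 | 65.8% |
| 0.245 | 30% gain nothing, all measured (0.7 × 0.35) | Φ(2.072 − 1.960) = 54.4% |

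**4. Baseline adjustment, 100 per arm, two-sided, d = 0.35.** If the ANCOVA adjusts for baseline CES-D, the residual SD becomes √(1 − r²). For an assumed baseline-outcome correlation r of 0.3, 0.4, 0.5 and 0.6, power is 73.7%, 77.0%, 81.5% and 87.2%.

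**5. The effect the trial expects, 100 per arm, two-sided.**
- d = 0.5: Φ(3.536 − 1.960) = 94.2%.
- d = 0.6: Φ(4.243 − 1.960) = 98.9%.

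**The case against.** The strongest reply is that nothing is miscalculated or hidden. The article prints the one-sided condition beside the figure, and the figure reproduces. It never calls the analyses two-sided: that is inferred from the F-tests and from the wording about different scores. The hypothesis is directional, a contrast with one degree of freedom can be tested one-sided, and a SAP could settle the matter.

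Much of this stands. There is no arithmetic error, and two-sidedness is an inference. But a directional expectation is routinely tested two-sided, and the tests actually described are non-directional. The article fixes a one-sided basis in one section and describes a different kind of test in another, so this is a mismatch between two stated things, not a detail left to a SAP.

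Two stronger readings are tempting and should be resisted:

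- **That power as planned is 69% or lower.** The 69% applies to 100 analysed per arm. With all 143 analysed and an undiluted 0.35 it is about 84%, and baseline adjustment also raises power. Power below 69% requires an added assumption, such as dilution of the effect.
- **That 0.35 is a completers-only effect.** The text does not say so. The 30% covers non-completion or exclusion and is applied to both arms, although wait-list patients have no course to complete in the first 12 weeks. Loss of outcome data fits both arms at least as well, and inflating to 143 is then an ordinary attrition allowance.

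The practical stakes are also limited. Even if the expected 0.5 were diluted by a zero benefit in 30%, the result is 0.7 × 0.5 = 0.35, which has 84% two-sided power with 143 per arm analysed.

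It is fair to say that an abstract abbreviates. Still, dropping the one-sided condition leaves a claim that does not hold for a two-sided test at 100 analysed per arm.

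**Conclusion.** The concern holds as a mismatch between the power statement and the analysis described. The 80% at 0.35 with 100 per arm is the power of a one-sided 5% test. For the two-sided 5% test that the analysis wording implies, the same 100 per arm gives about 69%, 80% power is reached at about 0.40, and 0.35 needs about 130 analysed per arm. These figures rest on the article's own inputs plus the inference that the F-tests will be judged two-sided at 5%.

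Under intention to treat with 143 per arm, power at 0.35 cannot be fixed more closely than about 54% to 84%. The upper end assumes no dilution. The lower end assumes that 0.35 is the effect without the 30%, that the 30% gain nothing, and that all of them are measured.

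The weight is moderate. A headline design figure does not match the test described, but at the expected effect of 0.5 to 0.6 two-sided power with 100 per arm is 94% to 99%, so the sample size is not undermined.

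**What to change.** 1. In the Power calculation section, restate the power for a two-sided 5% test: with 100 analysed per arm, 80% power for an effect size of 0.40, 69% for 0.35, and 94% or more at the expected 0.5 to 0.6.
2. In the Statistical Analyses section, state the sidedness and alpha of the primary test so that the two sections agree. If a one-sided 5% test really is intended, say so there and acknowledge the 5% false-positive rate in favour of the course.
3. Correct the abstract to match.
4. Say whether 0.35 is the intention-to-treat effect, and whether the 30% are patients without outcome data or patients who stop the course but are still measured. If adjustment for baseline CES-D is to be counted towards power, state the assumed correlation.

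The cost is a few sentences and a slightly less favourable detectable effect, 0.40 in place of 0.35. No extra patients are needed.

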## Discussion

### Strengths and Limitations

To the best of our knowledge, this randomised controlled trial will be the first to test the effects of a web-based CBT self-help course for people with diabetes and co-morbid depression. The intervention builds on an existing course that has shown to be feasible and effective to help improve mood in the general population [31]. Our trial is sufficiently powered to allow for conclusions as to its short-term effectiveness (6 months). In view of the "lenient" inclusion and exclusion criteria we will apply, the study is expected to have high external validity.

An obvious limitation of this trial is the fact that only people with access to the Internet and sufficient computer skills can be included. Overall, an estimated 82% of the Dutch households are online in 2007, but access to Internet among the elderly is much lower [21] and as a consequence this group may therefore be under represented in our study.

Inclusion and exclusion criteria are clearly stated on the website. This has the potential disadvantage that people can pretend to have certain characteristics in order to qualify or they can deny having "exclusion criteria". However, this response tendency may be diminished by the fact that patients are being made aware that we inform their GP's of their participation in the study and that we will be in contact with their treating physician concerning their HbA1c results.

As the post-treatment assessment will be done directly after treatment and up till 6 months follow-up, no conclusions can be drawn about the long-term effects of the intervention. Therefore, after 6 months, patients will be asked to give permission for supplemental follow-up measurements at one and two years after completion of the course. These results will be analysed at a later stage and are not part of this project.

Although web-based administration of questionnaires is widely used, we should remind ourselves that the psychometric properties of internet-administered questionnaires may not be equal to those of paper-and-pencil versions [32]. On the other hand, in an earlier study we have found that the paper-and-pencil and the computerised versions of a short psychological well-being questionnaire appeared to be equivalent [33]. The major difference appears to be that respondents are more honest and revealing when filling out via the Internet, resulting in a relatively higher reported level of symptomatology. We have therefore chosen to confirm or decline the diagnosis of depression by a telephone administered diagnostic interview (CIDI). Our study will show if such diagnostic procedure is required in future projects applying W-CBT in order to reduce the risk of 'false positives'.

Also the psychometric properties of the following on-line questionnaires will be examined and compared to the paper-and-pencil versions: the PAID, SF-12 and the ADSCI.

We hypothesise that improved mood will be associated with improved diabetes self-management and we will test whether W-CBT has favourable effects on self-reported diabetes self-care behaviours, using the Amsterdam Diabetes Self-care Inventory (ADSCI) that was developed by our team and used in previous trials [12,13,34]. The psychometric properties of the Amsterdam Diabetes Self Care Inventory (ADSCI) have not yet been published, but a report on the validity and reliability of the scale is planned based on data on file.

Ethical and practical considerations have led us to decide that all participants are allowed to use additional mental health care (MHC) services during the trial. Usage of additional services therefore is a potential confounder that will be measured and taken into account in the statistical analyses.

Drop-out is often a problem in web-based therapy trials. In adapting the generic coping with depression course to the needs of people with diabetes, we expect to reduce drop-out. In an attempt to further reduce the attrition rate, support e-mails will be send out to participants by their coach, to encourage them to stay involved in the course. Likewise, those in the waiting list condition will receive e-mails aimed to maintain contact and encourage them to participate.

The study protocol was approved by the VU University Medical Centre ethics committee, which is certified by the Central Committee on Research involving Human Subjects in the Netherlands.

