## Methods/Design

### Study Design

We chose a two-arm randomised controlled trial (RCT) design; including 286 patients (143/143) (see power calculation). Measurements are scheduled at six points in time in the intervention group: at baseline, directly after completing the web-based intervention, and at 1, 3, 4 and 6 months follow-up. In the control group the same six measurements are scheduled with two additional measurements at 8 and 12 weeks after randomization (see flow chart, Figure 1).

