#### Control group

Control group patients will receive an e-mail in which they are informed of the randomisation result, which means they will start the course after 12 weeks. To reduce the risk of loss of interest; participants placed on the waiting-list will automatically receive weekly protocollised e-mails with motivating, positive feedback to enforce them to remain involved in the study.

After eight weeks they are invited per e-mail to fill in the questionnaires again. Twelve weeks after randomization patients will undergo a second screening (using the CES-D-score ≥ 16 as a first screener for depression and additionally the CIDI interview) to confirm depression. If still eligible, the patient is invited to follow the course. Patients, who do not qualify, i.e. show (spontaneous) remission, are excluded at this point. Patients who developed suicidal ideation during the 12 weeks waiting period, are offered the opportunity to have an appointment with a diabetes psychologist of the VU University Medical Centre or a colleague nearby in case the distance from the participant's home to the VUMC should be problematic.

The effectiveness of the intervention is determined directly after completing the web-based intervention up till 6 months follow-up (see Consort flow chart in Figure 1).

If the depression has deteriorated at the end of the course, as indicated by the scores of the CES-D, a consultation with a diabetes psychologist at the VU Medical Centre is offered to the patient. In agreement with their General Practitioner a decision will be made about further treatment or hospitalization.

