### Outcome Assessment

#### Primary outcome measures

Primary outcome measure is the level of depression, measured by the online administered self-reported depression questionnaire Center for Epidemiological Studies Depression scale (CES-D) [26] at baseline, directly after completion of the course and at one and six months follow-up.

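### Six months is presented as a powered primary result, but the wait-list control is untreated only until week 12, so the 6-month effect against no treatment is not identified by the randomisation

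*Protocol article*

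**What the plan says.** Three places in the protocol article carry the effectiveness claim to 6 months.

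- Primary outcome measures sets the CES-D at baseline, "directly after completion of the course and at one and six months follow-up".
- Control group: "The effectiveness of the intervention is determined directly after completing the web-based intervention up till 6 months follow-up".
- Strengths and Limitations: "Our trial is sufficiently powered to allow for conclusions as to its short-term effectiveness (6 months". The same section concedes a limit only for effects later than 6 months.

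The wait-list is shorter than that. The abstract says: "Patients in the control condition are placed on a waiting list, and follow the course 12 weeks after randomisation". Study Design adds: "In the control group the same six measurements are scheduled with two additional measurements at 8 and 12 weeks after randomization". Under Control group, controls are re-screened at week 12. Those still depressed are invited to take the course, and those in remission are excluded.

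Power calculation defines the effect size as "the difference between the control group and the intervention group after the intervention, divided by the pooled standard deviation" and states: "With 100/100 patients the study is powered to detect an ES of 0.35 (one-sided), with a power of 80% (α = 0.05". Statistical Analyses plans two parts. The first is a between-group analysis of the direct effect, with a time-by-group ANOVA and ANCOVAs at time points that are not named. The second is a pre-post GEE in everyone who has received the course.

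**The concern.** A wait-list trial estimates the effect against no treatment only while the wait-list arm is waiting. Here that period ends at week 12, yet the primary outcome, the stated window of effectiveness and the power claim all extend to 6 months. Nothing in the article limits the randomised comparison to the waiting period or says that the 6-month result is uncontrolled. Because the only acknowledged limit lies beyond 6 months, a reader is led to take the 6-month result as controlled and adequately powered.

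At stake is the main conclusion. A 6-month group difference would compare early-treated patients with patients who have since been offered the same course. A 6-month within-patient change would have no control at all.

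**Working it through.** **1. The plan's own figure.** Inputs from Power calculation: effect size d = 0.35, one-sided α = 0.05, power 80%, 100 per arm, 30% loss.

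- n per arm = 2(1.645 + 0.842)² / 0.35² ≈ 101, against 100 stated.
- Power at 100 per arm = Φ(0.35·√(100/2) − 1.645) = 79.7%.
- 100 / 0.70 ≈ 143 per arm, 286 in total.

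The figure reproduces. It belongs to a contrast of treated patients with untreated controls after the intervention.

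**2. The timeline, in weeks from randomisation.** Inputs: 8-week course, control course from week 12, one month = 365.25/12/7 = 4.35 weeks. Control follow-up is taken as tied to the controls' own course.

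| Visit | Intervention arm | Control arm, own course |
|---|---|---|
| End of course | 8 | 12 + 8 = 20 |
| 1 month | 12.3 | 24.3 |
| 3 months | 21.0 | 33.0 |
| 4 months | 25.4 | 37.4 |
| 6 months | 34.1 | 46.1 |

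Controls are also measured, untreated, at weeks 8 and 12. If 6 months were counted from randomisation instead, it would fall at week 26.1. On either count it comes after week 20, when a control who took the course on schedule would have finished. The gap from the end of the untreated period is 26.1 − 12 = 14.1 weeks or 34.1 − 12 = 22.1 weeks.

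**3. Primary-outcome times against the control.** Of the three post-baseline times, end of course (week 8) and one month (about week 12) have an untreated randomised comparator. Six months does not.

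**4. What happens to the power.** Assume 100 per arm are evaluable, the intervention arm keeps its 0.35 SD gain, and treated controls have gained a share f of it. Power is then Φ(0.35(1 − f)·√50 − 1.645).

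| f | Difference (SD) | Power |
|---|---|---|
| 0 | 0.35 | 79.7% |
| 25% | 0.2625 | 58.4% |
| 50% | 0.175 | 34.2% |
| 75% | 0.0875 | 15.2% |
| 100% | 0 | 5% (α) |

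The shares are assumptions, since the article gives no figure for them. The stated 80% carries over to 6 months only if controls gain nothing from the course.

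**5. Direction of distortion.** Treating controls shrinks the between-group difference. Excluding remitted controls at week 12, with no matching removal in the intervention arm, leaves a more depressed control group and pushes the other way. It also conflicts with the intention-to-treat principle in Statistical Analyses. The table in step 4 leaves this second force out, and the net direction is unknown.

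**6. The pre-post GEE.** Patients enter with a CES-D score of 16 or more, and the article itself expects some spontaneous remission. Change from before the course to 6 months therefore mixes the course effect with remission and regression to the mean. No comparator separates them, and the power calculation does not cover this analysis.

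**The case against.** The strongest defence is that the plan already makes the separation. Statistical Analyses distinguishes a direct effect, tested between groups, from a pre-post analysis of everyone treated, and Power calculation ties the effect size to the difference after the intervention. On that reading the randomised contrast is short-term, later visits are within-patient data, and delayed access is simply what a wait-list design means. This partly stands. The design itself is not at fault and the authors show awareness of its limit. But the ANOVA and ANCOVA times are not restricted to the waiting period, and the three 6-month statements contradict the narrower reading.

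Some stronger readings are tempting, and the documents do not support them.

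- A reader might infer that nothing at 6 months can be estimated from the randomisation. What is lost is the effect against no treatment. Under the schedule in step 2, the intervention arm's visits at 3, 4 and 6 months lie within about a week of the controls' visits at end of course, 1 month and 3 months. An immediate-versus-delayed contrast could therefore be near-matched in time, subject to the week-12 exclusions. Figure 1, which holds the exact schedule, is not shown.
- A reader might infer that a late group difference must be diluted towards zero. The exclusion of remitted controls works against this.
- A reader might infer that most of the primary outcome is uncontrolled. Only one of its three post-baseline times is.
- A reader might infer that week 8 must be the sole primary time. Week 12 also has an untreated comparator, so that choice is partly preference.

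**Conclusion.** The 6-month claim is wrong as written. Six months falls 14 to 22 weeks after the last untreated control measurement, so the randomisation does not identify the effect against no treatment at that time, and the power calculation does not support a conclusion about it. This rests only on the stated 12-week wait and 8-week course, and holds whether follow-up is counted from the end of the course or from randomisation. The loss of power shown above depends on assumed catch-up shares and is an illustration, not an estimate. The bias in any later group comparison has no established direction. The randomised comparisons at weeks 8 and 12, and the sample size for the end-of-course contrast, are unaffected.

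**What to change.** - **Statistical Analyses:** limit the between-group ANOVA, ANCOVAs and Cohen's d to baseline, week 8 and week 12. Identify the end-of-course contrast at week 8 as the one the power statement refers to.
- **Primary outcome measures:** take six months out of the controlled primary outcome. Report the 3-, 4- and 6-month data, including the pre-post GEE, as uncontrolled follow-up.
- **Control group, and Strengths and Limitations:** reword to say that the trial is powered for the effect at the end of the course, with no comparison against untreated controls beyond 12 weeks.

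The change is in wording and analysis scope and needs no extra patients or visits. The cost is a narrower claim: effectiveness at the end of the course and about one month later, with maintenance to 6 months described but not tested against a control.

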### Intervention development and trial design

The Dutch version of the manual-based self-help course named 'Coping with Depression' ('In de put, uit de put') has been adapted as web-based intervention ('Kleur je Leven') [23,24]. This intervention has been adjusted further by our team to fit the needs of patients with diabetes ('Diabetergestemd'). Based on our research, clinical experience and input from an expert panel of diabetes patients, the following topics were incorporated: managing 'poor' test results, uncertainty about blood glucose fluctuations and negative emotions, communication with health care professionals, talking about diabetes with others, the burden of daily self-management, and coping with diabetes-related worries (e.g. about hypoglycaemia and late complications). The course consists of 8 consecutive weekly lessons. The course will provide information, practice examples, exercises/self-tests and homework assignments. The web-based course is delivered on an individual basis. Patients weekly receive (protocollized) feedback on their homework assignments from their coaches by e-mail. The coaches are psychologists and residents in clinical psychology from the department of Medical Psychology of the VU medical centre, supervised by the research team. An internet-based group forum, which will be moderated by our team, is offered to participants to give them the opportunity to share experiences, provide support and discuss issues related to depression and diabetes [25]. In the forum, specific treatment issues (e.g. related to oral medication or insulin) may not apply to all participants, but this should not be problematic. Rather, the mix of disease types and experiences can serve to illustrate the common features of diabetes and depression (thoughts, emotions and behaviors), while respecting individual differences.

It will be clearly stated that during the course of the study, all participants are allowed to make use of additional mental health care services if they feel a need to do so.

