#### Covariates

Additionally, information on potentially confounding factors and effect modifiers will be collected by means of self-report: socio-demographic data (age, gender, marital status, highest level of completed education, and current occupation), lifestyle issues (smoking, body mass index (BMI), substance/alcohol abuse), data on diabetes (type of diabetes, duration, treatment regimen, co-morbidity) and additional mental health care consumption.

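### Mental health care used during the trial is classed as a confounder to be accounted for; it follows randomisation, and adjusting the between-arm comparison for it can bias the intention-to-treat effect in either direction

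*Protocol article*

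**What the plan says.** Four parts of the protocol article bear on this.

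- **Discussion, Strengths and Limitations.** It states that "all participants are allowed to use additional mental health care (MHC) services during the trial" and then draws the consequence: "Usage of additional services therefore is a potential confounder that will be measured and taken into account in the statistical analyses". The inference concerns use during the trial, not use before it.
- **Covariates.** The section opens by saying that "information on potentially confounding factors and effect modifiers will be collected by means of self-report". Its list starts with age, gender and similar fixed characteristics and ends with "additional mental health care consumption". It does not say whether this last item is meant as a confounder or as an effect modifier, or at what time it is measured.
- **Intervention development and trial design.** Use is at the participant's discretion: "all participants are allowed to make use of additional mental health care services if they feel a need to do so".
- **Statistical Analyses.** "Analyses will be conducted according to the intention to treat principle". The ANOVA has time and group as its independent variables. The ANCOVA comparing the groups is run "with correction for potential confounders at baseline". A second analysis, by GEE, looks at change from before to after the course in everyone who received it. Extra care use is not mentioned in this section.

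No section confines the handling of extra care to a sensitivity, supplementary or descriptive analysis.

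**The concern.** A confounder of a randomised comparison would have to precede allocation. Care sought during the trial comes after it and can be a consequence of it: a patient told to wait 12 weeks has a reason to look elsewhere, and a patient whose mood has improved has less reason to. Conditioning on such a variable can do two things. If the extra care works, adjustment removes its contribution from the contrast, so the estimate no longer describes the total effect of allocation. If unmeasured severity drives both care-seeking and outcome, adjustment compares patients of unequal prognosis across arms.

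What is at stake is the CES-D comparison between arms. An estimate conditioned on later care is not the intention-to-treat effect that the plan promises, and a larger sample would not remove the difference. An analyst could also cite either the Discussion or the Statistical Analyses section to justify including or omitting the term after seeing the data.

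**Working it through.** **The plan's own figure.** The power calculation uses an effect size of 0.35, one-sided α = 0.05 and 80% power. n per arm = 2 × (1.645 + 0.842)² / 0.35² = 100.9, so 101; with 100 per arm, power is 0.797. Allowing for 30% loss, 100 / 0.70 = 142.9, so 143 per arm and 286 in all. The stated figures reproduce and are not in dispute. The effect of 0.35 SD serves below as the reference.

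**When adjustment matters.** For least squares, estimate without the care term = estimate with it + γ × (use in intervention arm − use in control arm), where γ is the coefficient of care use in the adjusted model. The gap is zero if use is equal in the arms or if γ is zero. Its sign depends on γ: positive if users of care are mainly those with poor prognosis, negative if the care itself lowers CES-D.

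**Inputs.** The documents give no rate of extra care and no effect of it. Everything below is assumed, and was evaluated in large simulated samples (400,000 to 1,000,000 patients). Care use follows a logistic model depending on arm and, where stated, on severity. Estimates are SDs in favour of the intervention.

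| Assumed setting | Use, control v intervention | Without care term | With care term | Change |
|---|---|---|---|---|
| Equal use | 26% v 26% | 0.35 | 0.35 | 0.00 |
| Care without effect, use linked to severity (log-odds slope 0.8; severity explains 25% of variance) | 26% v 19% | 0.35 | 0.33 | −0.02 |
| Same | 26% v 14% | 0.35 | 0.31 | −0.04 |
| Same | 26% v 10% | 0.35 | 0.29 | −0.06 |
| Care works (0.3 SD), use unrelated to severity | 23% v 8% | 0.31 | 0.35 | about +0.045 |
| Care works and use linked to severity | 26% v 10% | 0.30 | 0.29 | −0.01 |
| Care without effect, stronger severity link (severity explains 50% of variance; slope 0.8 to 1.0) | 32% v 27% | 0.35 | 0.32 | −0.03 |
| Same | 32% v 12% | 0.35 | 0.25 | −0.10 |
| Same | 33% v 7% | 0.35 | 0.19 to 0.20 | about −0.15 |

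The identity can be checked on the 32% v 12% row. On the CES-D scale, −0.35 = −0.25 + γ × (0.12 − 0.32), so γ = 0.10 / 0.20 = 0.50: users of care score half an SD worse, although the care does nothing.

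**With a baseline severity score in the model.** If its squared correlation with severity is 0.7, 32% v 12% gives 0.32 (0.35 − 0.32 = 0.03) and 33% v 7% gives 0.30 (0.05). If the correlation itself is only 0.5 to 0.7, about 31% v 12% gives 0.28 to 0.30 (a gap of 0.05 to 0.07) and about 32% v 7% gives 0.23 to 0.27 (0.08 to 0.12). If the extra care also helps by 0.3 SD at 32% v 12%, the total effect of allocation is 0.35 − 0.3 × (0.32 − 0.12) = 0.29. The model with care use and the stronger baseline score then returns 0.32, so the distortion is upward.

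**Consequences for the test.** In the milder severity-linked rows (0.33, 0.31, 0.29), one-sided power at 100 per arm falls from about 80% to about 75%, 71% and 66%, holding the standard error at √(2/100). With no true effect and use of 26% v 10%, adjustment creates an apparent effect of about 0.055 SD against the intervention.

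**The case against.** The strongest reply is that the plan does not commit to the harmful analysis. The Discussion sentence names no model. The Statistical Analyses section, which is the operative text, restricts the ANCOVA to baseline confounders and never mentions extra care. Read literally, it already does what one would ask for. The Covariates section speaks only of collecting the information. There is also a proper place for the variable: the pre-post GEE is not a randomised comparison, and concurrent care is a genuine rival explanation for change seen there. Finally, the article condenses a fuller protocol.

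Much of this stands. A reader might infer that the primary between-arm analysis will be adjusted for later care and that its result is therefore biased. The document does not support that, because no between-arm model is said to contain the term. A reader might also infer that adjustment would hide a real effect by some 30%. That rests on one set of assumed rates with no baseline severity in the model; other equally admissible assumptions give no distortion or the opposite sign.

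What does not fall away is that the article affirmatively calls a post-randomisation variable a confounder, says it will be taken into account, and does not limit this to the GEE or to a supplementary analysis. That is a statement made, not a detail left out, and it sits badly with the baseline-only rule.

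**Conclusion.** The point holds as an inconsistency with a possible cost, not as a demonstrated bias. The Covariates and Strengths and Limitations sections treat care used during the trial as a confounder; the Statistical Analyses section allows only baseline correction under intention to treat. If the former were followed in a between-arm model, the intention-to-treat effect could be distorted in either direction.

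Under the assumed rates, the distortion ranges from 0 to about 0.15 SD on an effect of 0.35 SD. With baseline severity in the model, it is about 0.03 to 0.07 SD at 12% against 31–32% use, and 0.05 to 0.12 SD at 7% against 32–33%, depending on how well the baseline score captures severity. These figures depend on use differing between arms, on the link between severity and care-seeking, and on whether the care works. The documents supply none of these. CES-D is measured at baseline, but the Statistical Analyses section does not name it as a covariate, so its inclusion is also an assumption. The point should be fixed, but it does not invalidate the design.

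**What to change.** Reconcile the Covariates, Statistical Analyses, and Strengths and Limitations sections by stating that:

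1. between-arm models adjust only for variables measured before randomisation; mental health care use recorded at baseline is acceptable;
2. care used during the trial is reported by arm;
3. any between-arm model that includes trial-period care is labelled supplementary and is not presented as the intention-to-treat effect;
4. trial-period care may still be considered in the non-randomised pre-post GEE.

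In the Discussion, the label of confounder should be dropped for trial-period use in the randomised comparison. The cost is a few sentences. The data are already to be collected, and the sample size of 143 per arm is unaffected.
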